#### Aim 1b

2.4.2

Communication, behavior, and quality of life will be measured using survey instruments determined by community-engagement and stakeholder participation, which will include a series of focus groups of caregivers, advocacy group members, and clinicians. The rationale, methodology, and results of the focus group input will be documented and reported. The goal is for surveys to be available in English and Spanish.

Surveys selected *a priori* to include in the focus group discussions include and are not limited to the following for each domain.

Communication: The Communication Matrix, Communication and Symbolic Behavior Scales.

Behavior: Adaptive Behavior Assessment System, Aberrant Behavior Checklist, Vineland 3.

Quality of Life: Quality of Life Inventory-Disability Questionnaire, CDKL-5 Severity Assessment.

Final selection of the validated survey instruments will be made by synthesizing the input from the focus groups, which will evaluate relevance and importance to families with lived experience, as well as comprehensibility and feasibility of completing the surveys, including cognitive load, validity, and time burden.

#### Aim 2

2.4.3

Data on epilepsy surgery and anti-seizure medication prescriptions will be extracted from the PCORnet® data marts of all 18 sites from a 7-year period (January 1, 2016, to December 31, 2022). This period will be extended when additional years are available, and the maximum index date will be moved accordingly to 1 year before the end of the data. Epilepsy surgery will include cranial epilepsy surgery, CC, VNS, deep brain stimulation (DBS), and responsive neurostimulation (RNS). Patient data such as center, age, race, ethnicity, health insurance, and medical complexity will also be extracted.

### Sample size estimates

2.5

Preliminary data exploration across the 7 high-intensity sites identified an average of over 200 pediatric patients with LGS per site. Based on this, we anticipate a total sample size of more than 3,600 with ICD-10 diagnosis code G40.81x and, after sampling, chart review, and recruitment, approximately 464 participants for Aim 1b. We expect that approximately one-third will be in the surgery arm.

### Data analysis

2.6

#### Aim 1a

2.6.1

Agreement before and after consensus will be quantified with Cohen’s Kappa. The gold standard diagnosis of LGS will serve as the binary outcome variable, which is inclusive of either classic LGS or pragmatic LGS. We will develop computable phenotype models containing candidate factors available in EHR repository data (such as diagnosis codes, medications, and combinations thereof) that may discriminate between patients with and without LGS. We will compute the sensitivity, specificity, and the area under the curve. We anticipate identifying three computable phenotypes: one that optimizes sensitivity while maintaining acceptable specificity, one that optimizes specificity while maintaining acceptable sensitivity, and one that balances the two. Our goal is that this work would inform and could be applied in the selection of future study cohorts based on EHR or administrative data.

To test the computable phenotypes further, we will perform our primary analysis of ED and inpatient admissions with our gold standard definition of LGS and with each of the computable phenotype definitions. The computable phenotype that provides the least distortion from that measured using the gold standard may be used as the primary computable phenotype; however, we anticipate replicating all analyses with all computable phenotypes to account for the possibility that unanticipated multivariable interaction, or other issues perhaps related to data quality or completeness, may affect the results.

The primary analyses will compare epilepsy surgery (CC or VNS, CC alone, VNS alone) to the addition of another LGS-approved medication. We also will compare CC to VNS. While CC and VNS are the most common surgeries, we will also explore all epilepsy surgeries including cranial epilepsy surgery, CC, VNS, DBS, and RNS to addition of another LGS-approved medication, to understand VNS and CC in the spectrum of care. We will use a generalized linear mixed model with Poisson distribution and log link to compare the frequency of ED visits and inpatient admissions in the 6 months post-intervention. To guard against any potential biases in the selection of the type of surgical therapy or of surgery versus medication that might arise due to medical complexity, we will employ inverse probability of treatment weighting (IPTW), which uses the propensity score/conditional probability to balance baseline patient characteristics across different treatment groups. Treatment selection will be modeled with a logistic regression using information available at the time the decision is made like age, sex, pediatric complex chronic conditions (PCCC) (39), and anti-seizure medication use. The inverse of the resulting probability will be used to weight each individual in regression models for the outcomes. PCCC scores, reflecting medical complexity, will be calculated from existing data provided by each site. Based on our knowledge of and experience with LGS and its treatment, we do not expect large differences between the patients receiving the different types of therapies. We will describe what the differences are that appear to influence the selective use of these different therapies.

A random site effect will account for clustering within sites. Robust standard errors will be used to control for mild violation of distributional assumptions. In the case of severe violations, a Negative Binomial or zero-inflated Poisson model may also be considered. We will report the conditional rate ratios that estimate the expected rates of ED visits and separate hospitalizations in the surgery arm compared to the medication arm for the 1-year and 2-year periods following intervention. Additionally, a combined variable representing overall emergency healthcare utilization, including both ED visits and inpatient admissions, will be considered.

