## Introduction

1

Lennox–Gastaut Syndrome (LGS) is a severe developmental epileptic encephalopathy that affects an estimated 48,000 children and adults in the United States (US) (1). LGS is characterized by multiple seizure types, life-long treatment resistant seizures, developmental delay, cognitive and behavioral impairments, and early death (2–4). The onset of seizures is typically in the first 2 years of life, but the syndrome is often not fully recognizable until children are 3 to 5 years old (2, 5). Individuals with LGS have multiple types of seizures including tonic–clonic, tonic, and atonic seizures (2). Prolonged seizures are common and require the use of rescue medications, emergency department (ED) visits, and unplanned hospital admissions (6, 7).

LGS, although rare, accounts for a disproportionate amount of healthcare utilization and expenditures. It accounts for up to 10% of all childhood-onset epilepsies and 1–2% of all epilepsies; however, it represents one-fifth or more of treatment resistant pediatric epilepsy (2, 8–10). Among children and adults, expenditures are two or more times greater in association with LGS than with other forms of epilepsy (11), and all-cause mortality in young people with LGS is ten times that in the general population (3). In a survey about living with LGS, 75% of parents reported that their child experienced seizures every day in the prior week, 30% reported going to an ED at least once in the past 6 months, and 51% reported using rescue medication to stop a seizure in the past 6 months (7). In addition to the burdens created by seizures, people with LGS have a profound level of cognitive and physical impairment. A caregiver-driven survey of young people with severe epilepsies found that in the subgroup with LGS, 42% did not walk independently, 25% did not have functional hand grasp, 42% were entirely dependent on someone else for feeding, 55% did not effectively communicate, and 50% were nonverbal (4). This degree of impairment further increases medical burden and financial stress with hidden costs of care, and significantly impacts the quality of life of patients with LGS and their families (12, 13).

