### Inclusion and exclusion criteria

2.3

Although children in many research studies are defined as <18 or <21 years of age, in practice, children with severe epilepsies such as LGS often remain with their pediatric providers well into their third decade of life, because of severe disability, and may continue to have coverage up to age 26 through their parents’ health insurance plans. Patients in the cohort will have been less-than-or-equal-to 26 years old at the beginning of the study period.

Inclusion and exclusion criteria for Aims 1a, 1b, and 2 are shown in Table 1.

**Table 1 tab1:** Study inclusion and exclusion criteria.

Aims	Inclusion criteria	Exclusion criteria
Aim 1a	Patient has a validated diagnosis of LGS or meets one of the LGS computable phenotype definitions the study evaluated Index treatment occurred between 2016 and 2021: first epilepsy surgery or initiation of additional LGS-approved medication Patient received neurological care at a study site at least 1 year before intervention and 2 years after intervention at the site	Patient does not meet minimum follow up criteria for neurological care at the study site
Aim 1b	Patient has a validated diagnosis of LGS Patient is currently being treated at a study site Caregiver can participate in English or Spanish	
Aim 2	Computable phenotype for LGS based on Aim 1a	

LGS, Lennox–Gastaut syndrome.

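### The stated criteria for the LGS phenotypes do not show what share of a selected cohort truly has LGS; weighted positive predictive value should be added where the phenotype alone selects patients (Aim 2 and the light-touch sites)

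*Protocol article*

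**What the plan says.** Protocol article, section 2.6.1 (Data analysis, Aim 1a), names the accuracy measures: "We will compute the sensitivity, specificity, and the area under the curve". It anticipates three phenotypes: "one that optimizes sensitivity while maintaining acceptable specificity", "one that optimizes specificity while maintaining acceptable sensitivity", and a third that balances the two. No number is attached to what counts as acceptable.

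The same section adds a further test. The primary ED and inpatient analysis is run with the gold standard and with each phenotype, and then: "The computable phenotype that provides the least distortion from that measured using the gold standard may be used as the primary computable phenotype". It also says that "we anticipate replicating all analyses with all computable phenotypes".

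The phenotypes are used in three places:

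- **Aim 2.** The whole inclusion criterion in Table 1 (section 2.3) is "Computable phenotype for LGS based on Aim 1a".
- **The 11 light-touch sites.** Section 2.2 identifies their cohorts by phenotype; the chart review takes place at the 7 high-intensity sites.
- **Aim 1a.** Table 1 admits patients with a validated diagnosis or with any of the evaluated phenotypes.

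On how common LGS is, the Introduction says "It accounts for up to 10% of all childhood-onset epilepsies and 1–2% of all epilepsies", and that among difficult cases "it represents one-fifth or more of treatment resistant pediatric epilepsy".

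**The concern.** A phenotype that selects a cohort should be judged on the cohort it delivers. The non-LGS share of that cohort is 1 − PPV. PPV depends on sensitivity, on specificity and on the share of LGS among the patients screened. The first two, and the AUC, do not contain the third. The same pair of accuracy figures can therefore describe a clean cohort in one pool and a heavily mixed one in another.

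False positives are to be expected: section 3.1 itself notes that the features of LGS overlap with those of other severe epilepsies.

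The stake is highest in Aim 2. Its outputs are treatment use by center, age, race, ethnicity, insurance and medical complexity, together with comparative analyses across sites. If contamination differs between groups, misclassification alone can look like a disparity. If it differs between surgery and medication, it can look like a treatment effect.

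**Working it through.** **Inputs.** The article gives no PPV, no target sensitivity or specificity, and no LGS share for the screened pool, so there is no stated figure to reproduce. From the Introduction, the LGS share is at least 20% in treatment-resistant pediatric epilepsy and up to 10% in childhood-onset epilepsy. Shares of 30%, 50% and 70% are assumptions for a pool enriched by the LGS code G40.81x. All sensitivities (Se) and specificities (Sp) are assumptions.

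**Step 1: PPV.** With p the LGS share of the pool, PPV = p·Se / [p·Se + (1 − p)(1 − Sp)].

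For Se 0.90 and Sp 0.80:

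- p = 0.20: 0.18 / (0.18 + 0.16) = 0.529
- p = 0.50: 0.45 / (0.45 + 0.10) = 0.818
- p = 0.70: 0.63 / (0.63 + 0.06) = 0.913

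| LGS share of pool | Se 0.90, Sp 0.80 | Se 0.95, Sp 0.80 | Se 0.90, Sp 0.90 | Se 0.80, Sp 0.95 |
|---|---|---|---|---|
| 10% | 0.333 | 0.345 | 0.500 | 0.640 |
| 20% | 0.529 | 0.543 | 0.692 | 0.800 |
| 30% | 0.659 | 0.671 | 0.794 | 0.873 |
| 50% | 0.818 | 0.826 | 0.900 | 0.941 |
| 70% | 0.913 | 0.917 | 0.955 | 0.974 |

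The 10% row concerns childhood-onset epilepsy at large. It is a less likely setting than the rows below it, because the plan reviews LGS-coded patients and a sample with codes linked to intractable epilepsy.

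**Step 2: what an acceptable specificity would be.** For a PPV of t, Sp = 1 − p·Se·(1 − t) / [t·(1 − p)]. With Se 0.90 and t = 0.80 as an illustration:

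- p = 0.20: 1 − 0.036/0.64 = 0.944
- p = 0.50: 1 − 0.09/0.40 = 0.775

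The specificity needed for the same purity moves by about 17 percentage points with the pool. It cannot be set without reference to the pool.

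**Step 3: whether the distortion check would reveal contamination.** Assume a rate ratio of 0.70 in LGS, equal base rates, and the same mix in both arms. The observed ratio is PPV × 0.70 + (1 − PPV) × (ratio in non-LGS).

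- Non-LGS ratio 1.0, PPV 0.53: 0.371 + 0.47 = 0.841, a visible distortion.
- Non-LGS ratio 0.70, PPV 0.53: 0.371 + 0.329 = 0.70, no distortion although 47% of the cohort is not LGS.

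A small distortion of the rate ratio is therefore compatible with a heavily mixed cohort.

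**Step 4: effect on a utilization figure.** Assume surgery use of 33% in LGS and 10% in non-LGS, the same in every insurance group, with PPV 0.80 in one group and 0.54 in another.

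- First group: 0.80 × 33% + 0.20 × 10% = 28.4%
- Second group: 0.54 × 33% + 0.46 × 10% = 22.4%

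A gap of 6 percentage points appears with no true difference. The distortion check does not examine this kind of result.

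**The case against.** Several points on the other side are sound.

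**The three measures are not the only test.** A reader might infer that the phenotypes are judged on sensitivity, specificity and AUC alone. They are not: section 2.6.1 adds the comparison with the gold standard, which bears directly on the rate ratio and would pick up contamination that differs by arm. That stands. The check still leaves a gap. It is worded as a possibility, has no threshold, covers only the ED and inpatient contrast, and can be run only where charts were reviewed.

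**A cohort that is about half non-LGS is not established.** That reading needs an LGS share near 20%, and 20% is stated as a floor. In a pool rich in G40.81x codes the same accuracy gives a PPV of 0.82 or more. The sample size section counts patients with that code, which points towards enrichment. This stands, and it is why the conclusion is conditional.

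**Replication is a robustness check.** A reader might infer that the sensitivity-optimized cohort will be presented as the LGS result. The article gives replication a different purpose, namely to see whether results change with the definition, and one of the three definitions favors specificity. The 7-site comparison is also run in validated patients, and Aim 1b requires a validated diagnosis. All of this stands. But agreement or disagreement across phenotypes does not tell the reader which cohort is mostly LGS.

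**A condensed article need not list every metric.** Computing three measures does not rule out a fourth, and a fuller plan may include PPV. It cannot be said that PPV will not be calculated. What the article does fix is the rule for building the phenotypes and a rule for preferring one of them, and PPV has no part in either.

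**Conclusion.** The point holds in a limited form. As stated, the criteria for building and choosing phenotypes do not include the quantity that governs cohort purity, and this matters most for Aim 2 and the 11 light-touch sites, where the phenotype alone selects patients. The size cannot be determined from the article. At the assumed accuracy of 0.90 and 0.80, the non-LGS share is 47% at a 20% LGS share, 18% at 50% and 9% at 70%. The dilution and disparity figures rest on further assumptions and show only what is possible. The validated 7-site comparison in Aim 1a and the Aim 1b results are not affected. This is an inexpensive improvement to make before the phenotypes are fixed, not a flaw that undermines the study.

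**What to change.** 1. Add PPV to the existing criteria (sensitivity, specificity, AUC and least distortion) for choosing the primary phenotype for Aim 2 and the light-touch sites.
2. Weight it to the pool where the phenotype is applied. Section 2.4.1 reviews LGS-coded patients but only a sample of uncoded ones, so the raw validation-set PPV partly reflects the sampling ratio. Give each reviewed chart the inverse of its sampling fraction; PPV is then the weighted count of true LGS among the selected, divided by the weighted count selected. Sensitivity needs the same weights.
3. Use a low-PPV, sensitivity-optimized phenotype only as a sensitivity analysis. A fixed minimum PPV is debatable and is not essential to the proposal.
4. Report weighted PPV and sensitivity from the chart-reviewed patients by surgery versus medication and, where numbers allow, by insurance and race/ethnicity.

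The adjudicated charts already supply the diagnoses, so no new data collection is needed, but the sampling fractions must be recorded and used; the article does not give them. The downsides are a possibly smaller primary cohort, imprecise PPVs in small subgroups, and an untested assumption that PPV from the 7 reviewed sites carries over to the 11 unreviewed ones, which should be stated as a limitation.

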**Figure 2 fig2:**
[figure not shown]
LGS classification workflow in Aim 1a. CRCs, clinical research coordinators; EHR, electronic health record; LGS, Lennox–Gastaut syndrome.

Data on emergency healthcare utilization, as well as treatments and covariates, will be extracted from PCORnet® data marts of the 7 high-intensity sites. The data types include demographics, diagnoses and conditions, encounters, procedures, prescriptions, medication administrations, healthcare providers, and deaths. Seizure-related emergency healthcare utilization will be defined as the frequency per year of seizure-related ED visits and seizure-related inpatient admissions in the 2 years after intervention (surgery or medical), with adjustment for the rate during the year before intervention. A secondary analysis will be done for 1 year after intervention as well. The index date of the intervention will be defined between January 1, 2016, and December 31, 2021, as that of the first relevant surgery or (if there was no surgery) that of the first exposure to a third anti-seizure medication, with at least one of the three being among the seven LGS-approved medications listed above. To the extent possible, we will also control for dietary therapy as a variable collected by chart review and accessible by codes. We also will analyze all emergency healthcare visits and inpatient visits (with or without seizure diagnosis codes) and the subset for which there is a diagnosis of fracture, head trauma, lacerations/avulsions/contusions, burns, aspiration, aspiration pneumonia, or near drowning (37), as an expanded seizure-related definition. Subset analysis will be done on data from 2020 and 2021, the years of the COVID-19 pandemic (38).

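### The Aim 1a model sentence names a 6-month window that conflicts with the 2-year outcome (1 year secondary), leaving the primary model's window unclear

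*Protocol article*

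**What the plan says.** The protocol article gives a time window for Aim 1a emergency utilization in four places.

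- **Outcome definition (Section 2.4.1).** The outcome is a frequency per year of "seizure-related ED visits and seizure-related inpatient admissions in the 2 years after intervention", adjusted for the rate in the year before intervention. The shorter period is explicitly subordinate: "A secondary analysis will be done for 1 year after intervention as well".
- **Eligibility (Section 2.3, Table 1).** "Patient received neurological care at a study site at least 1 year before intervention and 2 years after intervention at the site".
- **Model (Section 2.6.1).** In the paragraph that introduces the primary analyses, the article states "We will use a generalized linear mixed model with Poisson distribution and log link", and the purpose given is to "compare the frequency of ED visits and inpatient admissions in the 6 months post-intervention".
- **Reporting (Section 2.6.1, next paragraph).** Conditional rate ratios will be given "in the surgery arm compared to the medication arm for the 1-year and 2-year periods following intervention".

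Section 2.6.1 also says that the primary analysis of ED visits and admissions will be repeated under each computable phenotype. The phenotype whose result departs least from the chart-validated result may become the primary one.

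**The concern.** The only outcome model planned by default for Aim 1a is tied to a window that appears nowhere in the outcome definition. The 6-month sentence is not marked as secondary, exploratory or preliminary, and it stands where the primary analyses are described. An analyst could follow that sentence or the outcome definition and reach different primary results, each with support in the text.

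Three things are at stake.

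- **Prespecification.** The data are retrospective, so results for every window can be computed from existing records. A window fixed in advance is the main protection against choosing one after the results are known.
- **What is estimated.** A 6-month and a 2-year rate ratio agree only if the treatment effect is constant over time. Precision differs as well.
- **Phenotype choice.** The rule for selecting the primary computable phenotype refers to the primary analysis. If that analysis has no clear window, neither does the rule.

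**Working it through.** **1. The windows side by side**

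| Place in the article | Window after intervention | Status given |
|---|---|---|
| Section 2.4.1, outcome definition | 2 years, as a yearly frequency | main definition |
| Section 2.4.1, next sentence | 1 year | secondary |
| Table 1, eligibility | 2 years of care | required |
| Section 2.6.1, model sentence | 6 months | none; in the primary-analysis paragraph |
| Section 2.6.1, reporting sentence | 1 year and 2 years | none |

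Four of the five entries fit together. The model sentence fits none of the others. The 6-month figures in the Introduction come from a cited parent survey and define no outcome of this study.

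**2. Is there a stated figure to reproduce?** No. The article gives no power, event rate or sample size for Aim 1a that depends on the window. The rest of this check is illustrative and rests on assumed rates and effects.

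**3. Share of the window.** 6/24 = 25% of the 2-year window; 6/12 = 50% of the 1-year window.

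**4. Precision**

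- Poisson, constant rate: the variance of the log rate ratio is inversely proportional to follow-up time. The SE ratio, 6 months against 2 years, is sqrt(24/6) = 2.0.
- Negative binomial, with μ events per year and dispersion k: SE ratio = sqrt[(1/(0.5μ) + k) / (1/(2μ) + k)].

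| Assumed μ per year | k = 0 | k = 1 | k = 2 |
|---|---|---|---|
| 0.5 | 2.0 | 1.58 | 1.41 |
| 1 | 2.0 | 1.41 | 1.26 |
| 2 | 2.0 | 1.26 | 1.15 |

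With overdispersion over this range, the 6-month SE is about 1.15 to 1.6 times the 2-year SE.

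**5. Target of estimation.** Let the rate ratio be a in months 0 to 6 and b afterwards, with a constant comparator rate. Over T months the rate ratio is [6a + (T − 6)b]/T.

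- a = 1.0, b = 0.7: 6 months 1.00; 1 year (6 + 4.2)/12 = 0.85; 2 years (6 + 12.6)/24 = 0.775.
- a = 0.7, b = 1.0: 6 months 0.70; 1 year (4.2 + 6)/12 = 0.85; 2 years (4.2 + 18)/24 = 0.925.
- a = b: the same value in all three windows.

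The choice of window can therefore move the estimate in either direction.

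**The case against.** The strongest reply is that the rest of the article points one way. The outcome definition, the eligibility rule and the promised rate ratios all use 1 or 2 years, so the 6-month phrase may simply be leftover text. That is plausible, but the article does not say so, and the phrase sits in the sentence an analyst would follow when building the model.

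The reply does rule out several stronger readings.

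- **That the main analysis fails to estimate the stated outcome, or discards three quarters of follow-up.** A reader might infer this from the model sentence alone. Section 2.6.1 also commits to rate ratios "for the 1-year and 2-year periods following intervention", which are the windows of the outcome definition. Estimation of the stated outcome is planned; what is unclear is which window the primary model uses.
- **That three windows compete to be primary.** Section 2.4.1 labels 1 year as secondary. Only 6 months competes with 2 years.
- **That a 6-month window is biased by recovery after surgery.** The article describes no such recovery effect on seizure-related visits, and its Introduction sets out risks for surgery and for medication alike.
- **That the loss of precision can be sized from the article.** The Introduction's 30% with an ED visit in 6 months is a parent-survey figure from outside this cohort. It does not count admissions and is not stated to be seizure-related. It cannot anchor a standard error here.

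**Conclusion.** The contradiction is real and concerns the primary comparative analysis. The model sentence in Section 2.6.1 conflicts with the outcome definition in Section 2.4.1, with the follow-up requirement in Table 1 and with the reporting sentence in its own section. The consequence is an unclear primary window, 6 months or 2 years, which carries over to the choice of primary computable phenotype.

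That conclusion rests on the text alone. The size of any effect does not. The 25% share is arithmetic, but the SE ratios (2.0 under Poisson, about 1.15 to 1.6 with the assumed overdispersion) and the shifts in rate ratio depend on assumed rates and effect patterns. They apply only if the 6-month sentence is followed literally. The wording should be corrected before the analysis is run.

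**What to change.** In the model sentence of Section 2.6.1, replace the 6-month window with 2 years post-intervention (primary) and 1 year (secondary). State in the same place that the model adjusts for the rate in the year before intervention, because Section 2.4.1 calls for the outcome "in the 2 years after intervention (surgery or medical), with adjustment for the rate during the year before intervention". How follow-up time enters the model is not fixed by Section 2.4.1 and can be left to the analysis plan.

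If a 6-month analysis is wanted, define it with the other outcomes in Section 2.4.1 and label it exploratory. The phenotype comparison in Section 2.6.1 should then refer to the 2-year analysis as the primary one.

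The cost is one amended sentence in the protocol. Any analysis plan, which is not at hand, should be checked for the same phrase. The change asks for no data beyond what the article's own 2-year definition and eligibility rule already require.

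### If the zero-inflated Poisson fallback is used, its usual rate ratio is not the ratio of expected rates that the plan promises for Aim 1a

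*Protocol article*

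**What the plan says.** The outcome, in Data collection, Aim 1a (2.4.1), is the "frequency per year of seizure-related ED visits and seizure-related inpatient admissions in the 2 years after intervention", adjusted for the rate in the year before. It covers all patients and is not restricted to those who remain at risk of an event.

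Data analysis, Aim 1a (2.6.1) gives the model: "We will use a generalized linear mixed model with Poisson distribution and log link to compare the frequency of ED visits and inpatient admissions". Clustering is handled thus: "A random site effect will account for clustering within sites". Robust standard errors are to cover mild departures from the distributional assumptions. For larger departures: "In the case of severe violations, a Negative Binomial or zero-inflated Poisson model may also be considered".

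The reporting sentence comes next and applies to whichever model is used: "We will report the conditional rate ratios that estimate the expected rates of ED visits and separate hospitalizations in the surgery arm", relative to the medication arm, for the 1-year and 2-year periods.

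The article does not say whether treatment would enter the zero part of a ZIP model, which ZIP coefficient would be tested, or how a ratio of expected rates would be obtained from a two-part model.

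**The concern.** The two fallbacks are named side by side under one reporting sentence, but they do not deliver the same quantity by default. A Negative Binomial model with log link keeps the ratio of expected rates as its treatment coefficient. A ZIP model splits patients into a class with no events and an at-risk class, and has a treatment coefficient in each part if treatment is entered in both. The one normally read as a rate ratio describes the at-risk class alone.

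Aim 1a asks which pathway reduces seizure-related emergency care. One plausible route is that more children have no emergency visits at all, and the count-part ratio drops that route. The null hypothesis changes too, from equal expected rates to equal rates among those still at risk. Because the article gives no explicit trigger for the switch, a change of model made after seeing the data could also change the question answered.

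**Working it through.** **Inputs from the article.** The model, the fallback, the reporting sentence and the outcome definition are as quoted above. Sample size estimates (2.5) says: "We expect that approximately one-third will be in the surgery arm". That sentence follows the Aim 1b figure and is used here only to set an allocation. The article gives no event rate, effect size, event-free share or significance level for Aim 1a, so there is no stated figure to reproduce.

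**Assumptions.** All values of π (event-free class share) and λ (at-risk mean count) are assumed, as is a two-sided 5% level. S is surgery and M is medication.

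**Step 1: the identity.** Under ZIP, E[Y] = (1 − π)λ. Hence

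- promised ratio = [(1 − π_S)/(1 − π_M)] × (λ_S/λ_M)
- count-part ratio = λ_S/λ_M

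They agree only when π_S = π_M.

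**Step 2: assumed values put in.**

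| π_M | π_S | λ_M | λ_S | Count-part ratio | Promised ratio |
|---|---|---|---|---|---|
| 0.3 | 0.5 | 2 | 2 | 1.00 | (0.5×2)/(0.7×2) = 0.71 |
| 0.5 | 0.6 | 2 | 2 | 1.00 | (0.4×2)/(0.5×2) = 0.80 |
| 0.4 | 0.6 | 3 | 3 | 1.00 | (0.4×3)/(0.6×3) = 0.67 |
| 0.3 | 0.5 | 2 | 2.4 | 1.20 | (0.5×2.4)/(0.7×2) = 0.86 |
| 0.4 | 0.6 | 3 | 4.5 | 1.50 | (0.4×4.5)/(0.6×3) = 1.00 |

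In the first three rows the effect is lost. In the fourth the direction reverses. In the fifth a difference appears where expected rates are equal.

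**Step 3: fitted models.** One large simulated data set used the first row (90,000 patients, one-third surgery, true ratio 0.714):

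- Poisson 0.70; Negative Binomial 0.70
- ZIP count coefficient, treatment in both parts: 1.01
- ZIP count coefficient, intercept-only zero part: 0.85
- ratio of (1 − π)λ from the ZIP fit with treatment in both parts: 0.70

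So the promised ratio can be recovered from ZIP by one added step. With an intercept-only zero part the effect is attenuated rather than lost.

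**Step 4: rejection rates**, first row, 300 replicates:

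| n | Robust Poisson | ZIP count coefficient | ZIP, intercept-only zero part | Combined ratio from ZIP |
|---|---|---|---|---|
| 300 | 58% | 7% | 28% | 45% |
| 464 | 75% | 7% | 33% | 63% |
| 1000 | 98% | 6% | 53% | 96% |

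The 464 is the article's Aim 1b figure, used only as a convenient size. The simulations omit the site effect, the treatment weighting and the baseline-rate adjustment.

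**Step 5: no event-free class at all.** With ordinary overdispersed counts and a ratio of expected rates of about 0.67, the ZIP count coefficient came out at about 0.72 to 0.74, a mild attenuation.

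**Step 6: does the article show that the fallback will be needed?** The Introduction cites a survey in which "30% reported going to an ED at least once in the past 6 months", so about 70% had none. A plain Poisson with mean −ln(0.70) = 0.36 gives exactly that share of zeros. At the same rate over 2 years (four half-years) the mean is 4 × 0.357 = 1.43, with exp(−1.43) = 24% zeros. The figure is therefore no evidence of zero inflation.

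**The case against.** The strongest reply is that the article never says the count coefficient will be reported. Its only commitment is to rate ratios of expected rates. Read literally, that already obliges the analysts to combine both ZIP parts, which Step 3 shows can be done. The fallback is optional wording, Negative Binomial is named first, the planned model is already Poisson with robust standard errors, and the ZIP specification could sit in an analysis plan not shown.

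Most of this stands. A reader might infer that the plan will test the at-risk rate, that surgery will therefore show a ratio of 1, or that the cited survey makes the fallback likely. The documents support none of these. A ratio of exactly 1 needs an effect confined to the event-free share, treatment in the zero part, and the count part reported alone. The survey figure needs no zero inflation, covers ED visits alone and is not limited to seizure-related ones. The rejection rates illustrate a mechanism and are not power estimates for this study.

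What does not stand is that nothing needs changing. The article pairs a named model with a reporting sentence that the model's usual rate ratio does not satisfy. The word conditional does not settle it: it most naturally means conditional on site, but under ZIP it can also be read as conditional on being at risk. An analysis plan that follows this text would inherit the mismatch.

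**Conclusion.** The point holds in a limited form. Poisson and Negative Binomial target the ratio of expected rates, and the usual ZIP rate ratio does not. If ZIP is used and its count coefficient is reported, the surgery effect may be attenuated (0.85 against 0.71), lost (1.00 against 0.71) or reversed (1.20 against 0.86), and a difference may appear where expected rates are equal (1.50 against 1.00). With ordinary overdispersion the distortion is smaller, about 0.72 to 0.74 against about 0.67. Every one of these sizes depends on assumed event-free shares and rates. The identity behind them does not. The primary Poisson analysis is untouched. The change is worth making because it costs little and keeps the estimand fixed if the model has to change.

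**What to change.** In Data analysis, Aim 1a (2.6.1), make Negative Binomial, or Poisson with robust standard errors, the fallback from which the reported rate ratio is taken. Add one clause: if a zero-inflated model is fitted, the tested and reported quantity is the ratio of overall expected rates, (1 − π)λ, surgery versus medication, from a marginalized zero-inflated model or by standardization over the study population with a bootstrap interval. Show the event-free share and the at-risk rate by arm as description only.

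No new data are needed. The cost is a sentence or two of wording and, only if a zero-inflated model is kept, slightly more programming.
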